### First day of treatment

#### Randomization

Each eligible patient will be randomly assigned to one of two groups: “A” and “B”. A random number list generated by SPSS statistical software version 18.0 (IBM Corporation, Armonk, NY, USA) (balanced for each six cases per study branch) will be used for the allocation to each group. Researchers from the statistical center will send the randomized list in a numbered, sealed, and opaque envelope to the researcher responsible for participant recruitment and group assignment.

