### Procedure

Figure 1 describes the trial protocol. The eligibility of prospective participants will be determined by a researcher who is not involved in the assessment or treatment of the participants. Ethical approval was obtained from the Balearic Islands Human Research Ethics Committee in July 2013 (CEI-IB, #IB 2077/13 PI).

Upon arrival at the Clinic for Pain Treatment, recruited patients will be informed once again about the trial objectives, and any questions or doubts that the patient might still have with respect to the study will be resolved. Patients will then be informed that they are testing a new EA technique for knee pain treatment. Placebo or sham acupuncture (SA) will not be mentioned to the patient during the interview or referred to in the informed consent form. Subjects will be placed into one of two study groups (with a strict 50 % probability), and to reinforce and encourage treatment follow-up, patients will be told that the effects are to be perceived over the medium- to long-term time frame. Patients will be re-assessed to ensure that they still comply with the selection criteria and that they have not acquired any new criteria for exclusion. Participants will provide informed consent in the first baseline visit (Table 1).

**Table 1 Tab1:** Planned visit schedule for treatment and follow-up, indicating visit number and frequency

	Visits									
	0	1st	2nd -7th	8th	9th	10th	11th	12th	13th-14th	15th
			(2 weekly /month)	(follow-up 1st month)	(2nd month)	(follow-up 3rd month)	(every 45 days)	(follow-up 6th month)	(every 2 months)	End of follow-up (1 year)

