#### Blinding

The patient codes of the double-blind study will be placed in numbered, sealed, and opaque envelopes. Researchers, personnel performing the interviews, statisticians, and participants will be blinded to patient allocation. Study groups will consist of the following, although patients will have no knowledge into which study branch they have been placed: the experimental group (A) receiving EA or the control group (B) receiving SA.

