## Discussion

The aim of the study is to measure the effectiveness of EA in alleviating OA knee pain. Effectiveness indicators should be the relief of pain, stiffness and functional disability of the knee, the improvement of quality of live and a reduction in medication use.

The principal challenge expected with this study is the difficulty of effectively blinding SA application in a manner that is believable or credible for the patient. For this reason, we will avoid using the terms “sham acupuncture” or “placebo” in the information letter and consent form. The attempt to blind the process will be done by explaining to the patient that a new pain treatment will be assessed and compared with other techniques (infiltrations and analgesic stimulation) and that the selected patients must have no history of acupuncture treatment. The literature reports that the non-penetrating SA method has been widely used and has also been validated for avoiding skin receptor stimulation in SA [36]. Disclosure of a patient’s group affiliation will be avoided so that they will not be able to share information among themselves or compare treatments. The only person who will have full knowledge of the applied treatment will be the acupuncturist, although he will remain blind to the rest of the details of the study.

A satisfaction questionnaire will be completed at the end of the study to assess whether the patients believe they have or have not received treatment. To avoid introducing bias that could be caused by the interference of the circadian rhythm in the beta-endorphin and cortisol levels, patients will always be scheduled for blood sampling at the same hour.

As has been shown, it would seem clear that the treatment of knee OA must be a multidisciplinary approach, as there is currently no treatment alone that may be considered beneficial in absolute terms.

Although there are studies showing the efficacy of acupuncture for the treatment of OA pain, the lack of a common methodology to apply the treatment design complicates the comparison of the results between studies.

In this article, we combine all of the methodological suggestions for acupuncture studies, attempting to minimize the biases that may result from study design. We intend to make a comparison with a placebo that would allow the hypothesis to be validated.

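### Concealment of allocation is not assured, and giving group assignment to the recruiting researcher contradicts the stated blinding

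*Protocol article*

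**What the plan says.** Three parts of the protocol article bear on this.

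- **Randomization** (under First day of treatment). A list generated in SPSS is "balanced for each six cases per study branch". It leaves the statistical centre in an envelope, in the singular, that is opaque, sealed and carries a number. It goes "to the researcher responsible for participant recruitment and group assignment", so one person holds both tasks.
- **Blinding.** Patient codes are put into envelopes of the same kind, here in the plural. The next sentence reads: "Researchers, personnel performing the interviews, statisticians, and participants will be blinded to patient allocation". The section then decodes the labels: "the experimental group (A) receiving EA or the control group (B) receiving SA".
- **Discussion.** "The only person who will have full knowledge of the applied treatment will be the acupuncturist".

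Two further places give context. The Procedure section leaves eligibility to "a researcher who is not involved in the assessment or treatment of the participants", which does not say whether that person is separate from recruitment or assignment. Table 1 puts eligibility, consent and the baseline outcomes at visit 0, and randomisation at visit 1.

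**The concern.** Concealment requires that whoever decides whether a patient enters cannot know or predict the next arm. Here the list is described as going to the person who recruits, and that person also assigns. Part of eligibility is a judgement: the inclusion criteria ask for at least moderate, clinically significant pain and set no numeric threshold. A recruiter with foreknowledge could, even without intent, influence who proceeds to randomisation and when.

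Both primary outcomes, VAS pain and WOMAC pain, are reported by the patient. If selection into arms took place, both could be biased, and adjustment for measured covariates could not be relied on to remove the bias. The Discussion names credible blinding as the main challenge of the trial, so the account of who knows the allocation should be free of contradiction.

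**Working it through.** The plan gives no figure for predictability. Its one calculated figure, the sample size, reproduces: 64 evaluable per arm, 64 / (1 − 0.20) = 80 per arm, 160 in total. This point does not change it.

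**Step 1. Two readings of the envelopes.** The Randomization section speaks of one list and one envelope. The Blinding section speaks of patient codes in several envelopes.

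| Reading | What the assigner learns | Agrees with blinded researchers? | Agrees with only the acupuncturist knowing? |
|---|---|---|---|
| One envelope holding the list | On opening it for patient 1, the other 160 − 1 = 159 allocations | No | No |
| One envelope per patient | Each patient's letter at assignment, hence the treatment | No | No |

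The second row fails because the letters are decoded in the protocol itself. It would hold only if the recruiter passed each envelope unopened to the acupuncturist. The article does not say so, and in that case the recruiter would not be the person assigning.

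**Step 2. Predictability of fixed blocks.** Inputs: 1:1 allocation, and balance at every six cases per branch. Read literally, this is six per arm, a block of 12 (m = 6). Read loosely, it is a block of 6 (m = 3). Assume the assigner knows the block boundaries and all earlier allocations in the block, guesses the arm with fewer patients so far, and tosses a coin when the arms are level.

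Expected correct guesses per block of 2m: m + ½ × (4^m / C(2m, m) − 1).

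- m = 6: 6 + ½ × (4096 / 924 − 1) = 6 + 1.72 = 7.72; 7.72 / 12 = 64.3%.
- m = 3: 3 + ½ × (64 / 20 − 1) = 3 + 1.10 = 4.10; 4.10 / 6 = 68.3%.

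Expected number of fully determined allocations at the end of a block: 2m / (m + 1).

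- m = 6: 12 / 7 = 1.71 per block, 14.3% of allocations.
- m = 3: 6 / 4 = 1.50 per block, 25.0% of allocations.

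Enumerating all 924 blocks of 12 and all 20 blocks of 6 gives the same results. Without knowledge of earlier allocations the rate is 50%. With the whole list open it is 100%.

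**The case against.** The strongest reply is that the article does describe a recognised concealment device. The sentence that sends the list specifies a sealed, opaque, numbered envelope, and the Blinding section repeats this in the plural. Numbering makes more sense for a series than for a single envelope, so one envelope per patient is a plausible reading. Table 1 already places consent and baseline measures before randomisation. The guess rates need an assigner who knows past allocations and block boundaries, and nothing says that the recruiter is told the block size.

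Much of this stands, and it rules out some stronger inferences:

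- A reader might infer that allocation is simply not concealed. The documents do not support that, because under the per-patient reading concealment before enrolment is provided for.
- A reader might infer that eligibility is re-checked at visit 1 by the person holding the list. The Procedure section describes a re-check but gives no visit number, and Table 1 ticks the criteria at visit 0 only. Nor does the article say that the assigner judges eligibility.
- A reader might infer that the statisticians are unblinded by a data set coded A and B. No section says how the analysis file is coded, and that is commonly left to a document not shown here.

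The reply does not remove the conflict of roles. The recipient is stated to perform group assignment, and whoever does that learns the arm under either reading of the envelopes.

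**Conclusion.** The point holds as a contradiction and as a gap in assurance. The assignment role in the Randomization section cannot be squared with the Blinding section or the Discussion, whichever reading of the envelopes is meant. Concealment itself is unsettled: lost from the second patient onward if one opened envelope holds the list, and provided for if envelopes are individual and opened only after enrolment.

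With individual envelopes, what remains is that an assigner who sees past allocations could predict the next one 64% (blocks of 12) or 68% (blocks of 6) of the time, against 50%. Those figures assume full knowledge of earlier allocations in a fixed block. The assigner's role makes the allocations available, but awareness of the block boundaries is an assumption. Nothing in the article shows that selection took place. The correction should be made, because following the Randomization section literally would expose upcoming allocations to the recruiter in a trial with patient-reported primary outcomes.

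**What to change.** Reconcile the Randomization, Blinding and Discussion sections so that they describe one procedure:

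- The statistical centre keeps the list.
- Each patient has one numbered, opaque, sealed envelope.
- Only the acupuncturist, who must know the treatment anyway, opens the next envelope. This happens at visit 1, after consent, the eligibility re-check and the baseline measures have been recorded.
- The recruiting researcher never holds the list and never learns an allocation. The Blinding section should name the acupuncturist as the exception to blinded researchers.
- Optionally, withhold the block size from recruiters, or vary it for the remaining patients.

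The Trial status section says recruitment is under way, so the change can apply to patients still to be enrolled, and the procedure used until then should be documented. The cost is a small change in who handles envelopes, with no extra staff. Varying the block size would also need a new list for the remaining patients.

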#### Blinding

The patient codes of the double-blind study will be placed in numbered, sealed, and opaque envelopes. Researchers, personnel performing the interviews, statisticians, and participants will be blinded to patient allocation. Study groups will consist of the following, although patients will have no knowledge into which study branch they have been placed: the experimental group (A) receiving EA or the control group (B) receiving SA.

#### Intervention

The treatment will be applied in eight sessions (two per week) for 1 month. Group A patients will receive the EA treatment, and group B will receive the SA treatment. Both groups will receive two weekly sessions for 4 weeks, then one session (each month) for the first 3 months, one session (each 45 days) until 6 months, and finally one session every 2 months until finalizing the study after a year’s time.

Treatments will be performed by the same acupuncturist, an anesthesiology specialist who has studied Traditional Chinese Medicine (TCM) at the University of Chinese Medicine, Beijing, China, holds a master’s degree in acupuncture from the University of León, Spain, and has more than 8 years of clinical experience in therapeutic pain management by acupuncture.

##### Experimental group (group A)

EA will be performed for a 20–30 min treatment session, and the patients will be semi-seated comfortably on a stretcher. A 0.30 × 30 mm needle will be used and will make a 10–30 mm insertion into the skin, depending on the patient’s constitution. Needle insertion points will be selected according to the TCM meridian theory for knee pain treatment. Upon insertion, EA will be applied by a biphasic pulse generator apparatus at a frequency of 3 Hz and at the maximum tolerable intensity. Table 2 shows the local and distal points: St 34 (*Liáng Qiū*), localized 2 cun proximal to the upper lateral border of the patella, in a groove of the vastus lateralis muscle; St 35 (*Dú Bí*), in the depression inferior to the patella and lateral to the patellar ligament; St 36 (*Zú Sān Lĭ*), one fingerbreadth lateral to the anterior crest of the tibia, on the tibialis anterior muscle; Lv 8 (*Qū Quán*), proximal to the medial end of the popliteal crease, in a depression anterior to the tendons of the semitendinosus and semimembranosus muscles; Sp 9 (*Yīn Líng Quán*), in a depression distal to the medial condyle of the tibia, at the junction of the shaft and the medial condyle; Sp 10 (*Xuè Hăi*), 2 cun proximal and slightly medial to the medial superior border of the patella, in a depression on the vastus medialis muscle; Ki 10 (*Yīn Gŭ*), at the medial end of the popliteal crease, between the tendons of the semimembranosus and semitendinosus muscles, on the level of the knee joint space; M-Le 16 (*Xi Yan*), inferior to the patella, medial and lateral to the patellar ligament; and M-Le 27 (*Hè Ding*), in the center of the upper border of the patella. As a distal point, St 44 (*Nèi Tíng*), between the second and third toes, proximal to the interdigital fold, will be used.

**Table 2 Tab2:** Framework of acupuncture points that should be selected when administering acupuncture treatments

Location	Acupuncture points	Description
Local points		
	St 34 (*Liáng Qiū*)	2 cun proximal to the upper lateral border of the patella, in a groove of the vastus lateralis muscle.
	St 35 (*Dú Bí*)	In the depression inferior to the patella and lateral to the patellar ligament.
	St 36 (*Zú Sān Lĭ*)	One fingerbreadth lateral to the anterior crest of the tibia, on the tibialis anterior muscle.
	Lv 8 (*Qū Quán*)	Proximal to the medial end of the popliteal crease, in a depression anterior to the tendons of the semitendinosus and semimembranosus muscles.
	Sp 9 (*Yīn Líng Quán*)	In a depression distal to the medial condyle of the tibia, at the junction of the shaft and the medial condyle.
	Sp 10 (*Xuè Hăi*)	2 cun proximal and slightly medial to the medial superior border of the patella, in a depression on the vastus medialis muscle.
	Ki 10 (*Yīn Gŭ*)	At the medial end of the popliteal crease, between the tendons of the semimembranosus and semitendinosus muscles, on the level of the knee joint space.
	M-Le 16 (*Xi Yan*)	Inferior to the patella, medial and lateral to the patellar ligament.
	M-Le 27 (*Hè Ding*)	In the center of the upper border of the patella.
Distal point		
	St 44 (*Nèi Tíng*)	Between the second and third toes, proximal to the interdigital fold.

The needles will be inserted through the same guide tube that will be used for the control group. The objective is for control patients to perceive the De-Qi sensation, which is like a tingling or numbness on the specific points punctured. Subsequently, EA will be used between *Xiyan* points and also to the points that the patient recalls as the area of pain. If both knees are affected, the same acupuncture points will be applied.

To ensure that the treatment procedures for the treatment and the control groups are as similar as possible, we will tape two guide tubes to two sham points at the abdominal area, approximately 3 cm lateral to and slightly above the umbilicus bilaterally. Immediately after, we will affix a pair of needles by adhesive tape to the surface at these same points though without needle insertion. This site was chosen for two reasons. First, these sites were at two meridians that are theoretically irrelevant to knee pain. Second, to facilitate blinding, we wanted to provide the participants of both groups the opportunity to be able to feel a sensation similar to the actual insertion of the needle.

##### Control group (group B)

A valid method of placebo acupuncture with non-insertion of the needle will be used for the control group [35]. Two needles will be inserted into the sham points of the abdominal area in the same position used for group A, approximately 3 cm lateral to and slightly above the umbilicus bilaterally, and then two pieces of adhesive tape will be immediately taped next to the needles. In addition, a mock plastic needle guide tube will be placed on the surface of each of the nine true points in the leg so that some discernable sensation will be produced; then a needle will be immediately applied without needle insertion to the dermal surface at each point and will be retained at this position for 20–30 min. These plastic guide tubes will be applied in the same manner as for group A in order to produce the same perceptible sensation.

The control group will receive the same session and schedule as group A. This will include the same active needle placements, although needle insertion will not occur at these nine points (local and distal points). Not only will the accessories of the EA equipment be connected in the same point in group A without electric stimulation, a mock transelectrical stimulation unit (which emits a “timer” sound and has a blinking light) will be attached to the sham needles at the knee.

To facilitate patient blinding for both groups, a screen will be placed below the abdomen to prevent participants from actually observing true or sham procedures at the knee area but at the same time will permit them to see the procedure that is being given in the abdominal area. It is important to state that this type of intervention will need some time for the results to be noted, and a thorough follow-up is necessary to avoid dropouts from both groups.

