**Methods/design:**

This study is a placebo-controlled, randomized, double-blind, parallel design trial. One hundred sixty out-patients who are more than 50 years old and who have osteoarthritis of the knee will be recruited from the island of Mallorca, Spain. Each participant will be randomly placed into one of two groups: (sham) electro-acupuncture non-insertion technique and real electro-acupuncture.

Acupuncture treatments will be the Traditional Chinese Medicine type. The patients will be evaluated after a period of 1 month (with two weekly sessions), 3 months (with one monthly session), 6 months (with one session every 45 days), and 1 year later with follow-up sessions at the end of the study (with one session every 2 months).

The primary outcomes will be based on the observed changes from the baseline of the visual analogue scale (VAS) and the Western Ontario and McMaster Universities Osteoarthritis Index (WOMAC) for pain measured at 12 weeks after the end of treatment.

Also to be included in the study are the possible changes in the secondary efficacy variables from baseline as assessed by the Short Form 36 version 2 health survey (patient-perceived quality of life), patient plasma cortisol and beta-endorphin levels at the different treatment stages, the Goldberg Anxiety and Depression Scale, pain medication use, functional capacity and stiffness (WOMAC subscales), and a VAS. These variables will be assessed at 1 month, 3 months, 6 months, and 1 year after study commencement.

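### The protocol has needles inserted at two visible abdominal points in controls but only taped to the skin there in group A, although it labels the sham as non-insertion

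*Protocol article*

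**What the plan says.** The Abstract (Methods/design) names the two groups as sham "electro-acupuncture non-insertion technique and real electro-acupuncture". The Background lists a sham that does not penetrate the skin among the methods the trial intends to apply. Under Control group (group B), the first sentence reads "A valid method of placebo acupuncture with non-insertion of the needle will be used for the control group". The next sentence reads "Two needles will be inserted into the sham points of the abdominal area in the same position used for group A", with tape then placed beside the needles.

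Under Experimental group (group A), the abdominal step is introduced with the purpose "To ensure that the treatment procedures for the treatment and the control groups are as similar as possible". Guide tubes are taped at the two abdominal points, and the acupuncturist is to "affix a pair of needles by adhesive tape to the surface at these same points though without needle insertion". One reason given for this site is to "provide the participants of both groups the opportunity to be able to feel a sensation similar to the actual insertion of the needle".

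The control-group section later limits non-insertion to the leg: "although needle insertion will not occur at these nine points (local and distal points". A screen hides the knee from patients in both groups but "will permit them to see the procedure that is being given in the abdominal area".

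**The concern.** These statements are operative instructions for what is physically done to patients, and they conflict. A matching step is described with insertion in one arm and without it in the other. A placebo introduced as non-insertion is then given two inserted needles in the following sentence.

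The identity of the comparator is at stake. The sham is the only control for the primary contrast, change in VAS and WOMAC pain. The Discussion supports the sham by citing validation of the non-penetrating method as a way to avoid stimulating skin receptors. That support does not extend to a sham that includes two penetrating needles. A reader of the results needs to know what electro-acupuncture was compared with, and the present text gives two answers.

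This is not a detail left to a fuller document. The article states both rules, and a statistical analysis plan would not decide which is right.

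**Working it through.** The plan gives no figure to reproduce and no formula applies. The check sets the sections side by side.

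| Site | Group A | Group B | Can patients see it? |
|---|---|---|---|
| Two abdominal points | Guide tubes and needles taped to the surface, no insertion | Needles inserted, tape placed beside them | Yes, both groups |
| Leg points | Needles inserted, current applied | Needles laid on the skin, mock stimulator | No, screened |

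The location of the abdominal points is worded alike in both sections, so the same points are meant.

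Three readings are possible. Each is tested against three statements: (i) the abdominal step makes the arms alike, (ii) the sham is non-insertion, and (iii) each arm's own paragraph is accurate.

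1. **The verb is loose wording for placed.** No abdominal insertion in either arm. (i) and (ii) hold. (iii) fails for the control-group sentence.
2. **The verb is literal and applies to controls only.** Two inserted needles per session in group B and none at those points in group A. (iii) holds. (i) fails. (ii) is false unless it is restricted to the leg.
3. **The group A paragraph is wrong and both arms have abdominal insertion.** (i) holds. (ii) is false unless restricted to the leg. (iii) fails for the group A paragraph.

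At least one statement is wrong under every reading, so the text needs correcting whichever is true.

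The wording does not choose between them. For the literal reading, the control-group section uses one verb for the abdominal needles and a contrasting description, contact without insertion, for the leg needles. It puts the tape next to the abdominal needles, and it later confines non-insertion to the leg: "although needle insertion will not occur at these nine points (local and distal points". For loose wording, the sentence immediately before promises non-insertion, the abdominal sentence refers back to the group A position, and the stated aim is that both groups feel something similar to insertion, which suggests that real insertion occurs in neither.

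**The case against.** The strongest defence is that the difference may be intended. A visible needle at the abdomen with the knee screened could serve to make the sham credible. Non-insertion would then describe the therapeutic points only, as the later wording about nine points suggests, and the Background item on non-penetrating sham could be met in that sense. The method is also attributed to a cited source that is not at hand. The two instructions stand under different arm headings, so an acupuncturist can carry out both, and the stated aim is similarity as far as possible, not identity.

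Much of this stands. It is not the case that the instructions cannot both be followed, and loose wording remains plausible. The defence still does not rescue the text. If insertion in controls is deliberate, the arms differ at points introduced to make them alike, and the label in the Abstract and in the control group's own opening sentence carries no restriction to the leg.

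A reader might infer that blinding is broken, that the pain contrast is biased in a known direction, or that control cortisol and beta-endorphin values are altered because post-baseline blood is drawn 5 min after treatment. The documents support none of these. Patients with an acupuncture history are excluded, patients are to be kept from comparing treatments, and the abdominal points were chosen as irrelevant to knee pain. No figure links abdominal needling to any outcome. Counting needles or blood samples over the trial would measure no harm.

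**Conclusion.** The point holds as an explicit contradiction in an operative rule, not as missing detail or a mere clerical matter. Taken as written, the control arm is penetrated at two visible points where the active arm is not, and the unqualified non-insertion label is false.

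The discrepancy is two needles per session in controls against none at the same points in group A under the literal reading. Under the loose-wording reading it is zero in both arms, and the harm is limited to a misdescribed sham. Which reading is true cannot be established from the protocol article. No size or direction of bias in VAS, WOMAC pain or hormone levels is claimed under any reading. The correction should be made because the sham defines the trial's only comparison and the change is small.

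**What to change.** First establish what is done at the abdomen in each arm. According to the Discussion, only the acupuncturist has full knowledge of the treatment given, so the question should go to that person through someone outside outcome assessment and analysis, to keep the blind.

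- **No insertion in either arm:** replace the control-group sentence with: *As in group A, guide tubes will be taped at the two abdominal points and a needle fixed to the surface at each, without insertion.*
- **Controls have already received abdominal insertion** (recruitment opened in January 2015 according to Trial status): keep the procedure as it is. In the protocol and the report, describe the comparator as non-penetrating at the nine leg points only, with two penetrating abdominal needles, and state whether group A received the same. If it did, correct the group A paragraph as well.

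The cost is one or a few sentences and a briefing of the single acupuncturist. The downside is that the sham may be slightly less credible if a real abdominal insertion was intended and is dropped. The expectation item that Table 1 schedules at 1, 3, 6 and 12 months, together with the questions on which treatment patients believe they receive, at 1 month and at study end, would help to show this.
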